## Abstract

**Background:**

Recurrent stroke is a major contributor to stroke-related disability and costs. Improving health-risk behaviours and mental health has the potential to significantly improve recovery, enhance health-related quality of life (HRQoL), independent living, and lower the risk of recurrent stroke. The primary aim will be to test the effectiveness of an online intervention to improve HRQoL among stroke survivors at 6 months’ follow-up. Programme effectiveness on four health behaviours, anxiety and depression, cost-effectiveness, and impact on other hospital admissions will also be assessed.

**Methods/design:**

An open-label randomised controlled trial is planned. A total of 530 adults will be recruited across one national and one regional stroke registry and block randomised to the intervention or minimal care control group. The intervention group will receive access to the online programme Prevent 2nd Stroke (P2S); the minimal care control group will receive an email with Internet addresses of generic health sites designed for the general population. The primary outcome, HRQoL, will be measured using the EuroQol-5D. A full analysis plan will compare between groups from baseline to follow-up.

**Discussion:**

A low-cost per user option to supplement current care, such as P2S, has the potential to increase HRQoL for stroke survivors, and reduce the risk of second stroke.

**Trial registration:**

Australian and New Zealand Clinical Trials Registry, ID: ACTRN12617001205325p. Registered on 17 August 2017.

**Electronic supplementary material:**

The online version of this article (10.1186/s13063-019-3604-0) contains supplementary material, which is available to authorized users.

## Background

Hypertension, smoking tobacco, low levels of physical activity, poor diet, and heavy levels of alcohol consumption are risk factors for recurrent stroke, [1] and can impact on health-related quality of life (HRQoL) [2–6]. Poor health behaviours can increase the risk of a second stroke due to their impact on each other, or being directly associated with the risk of a second stroke [7–12]. Further to these health-risk behaviours, higher rates of depression and anxiety have been found among stroke survivors and have been identified as barriers to stroke survivors seeking counselling, advice, and education to modify health-risk behaviours post stroke [13]. Depression and anxiety have also both been proposed to have a significant negative association with HRQoL [14–16].

Providing behavioural interventions, such as brief advice, education, and counselling to modify patient health-risk behaviours, is evidence-based best practice according to clinical guidelines for stroke management [17]. However, audits have found that only about half of all patients receive behavioural interventions at the time of discharge [18]. There are a number of reasons for this evidence-practice gap, including practitioner lack of training, confidence, and skills and time to provide counselling and advice [19].

An online intervention may be one way to address these barriers while meeting the APEASE criteria for designing scalable interventions of Affordability, Practicality, Effectiveness, and cost-effectiveness, Acceptability, Safety, and Equity [20]. In Australia, more than 86% of households report Internet access at home [21]. Surveys show that up to 80% of patients have an interest in supplementing clinician-delivered support with Internet-delivered information, [22] and reviews have consistently demonstrated the effectiveness of online interventions among comorbid populations for reducing pain, disability, depression, and anxiety [23–25].

### Aims

The primary aim of this study is to examine the effectiveness of an online healthy lifestyle intervention – Prevent 2nd Stroke (P2S) – at improving HRQoL among stroke survivors at 6 months’ follow-up. A secondary aim is to examine the cost-effectiveness of the intervention compared to usual care. Additional secondary aims are to examine the effect of the online P2S programme on:Four health behaviours (smoking, alcohol use, fruit and vegetable intake, and moderate physical activity)Mental health (depression and anxiety levels)Self-reported physical functioning and independent living, andHospital admission for recurrent stroke, myocardial infarction and all other causes

## Methods/design

### Design

A prospective, open, blinded end-point, randomised controlled trial (PeRSiST trial) with stroke survivors as the unit of randomisation will be conducted. Outcome assessments will be blinded. A flow chart of the trial design appears in Fig. 1. The protocol has been written following the Standard Protocol Items: Recommendations for Interventional Trials (SPIRIT) advice (see Additional file 1).

**Fig. 1 Fig1:**
[figure not shown]
Schematic of the Prevent Second Stroke Trial (PeRSiST) study trial design

### Setting

Participants will be recruited through two sources: (1) the Australian Stroke Clinical Registry (AuSCR) database, which is a national prospective opt-out enrolment registry for stroke and transient ischaemic attack (TIA) patients at 68 hospitals in six states of Australia, and (2) the Hunter Stroke Research Volunteer Register (HSRVR), this is a centralised database of people with stroke or TIA living in the Hunter region of the state of New South Wales who are willing to be contacted to participate in stroke research.

### Participants

#### Eligibility criteria

Individuals will be included if they: are aged 18 years and over; have been admitted to an AuSCR hospital for a first episode of care for acute stroke or TIA (indexed stroke event) *or* are registered with the HSRVR; are between 6 and 36 months post stroke; are sufficiently fluent in English; and have sufficient facility in Internet use via a home device (e.g. computer or tablet device) or are willing to use public Internet services (e.g. public library).

#### Exclusion criteria

Individuals will not be eligible to participate in the study if they have documented evidence of a previous stroke (second to the indexed stroke event) or experience disability at a level that may limit their use of the programme (determined using a score of ≤ 3 on the modified Rankin Scale) [26].

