### Randomisation

A random number generator embedded in the computer-assisted telephone interview (CATI) software will be used to allocate study participants to either receive the intervention or standard care after all baseline questions have been answered. Individuals will be randomised at a ratio of 1:1 in permuted blocks of randomly varying size (e.g. four and six), stratified by state (New South Wales, Queensland, Western Australia, Victoria/Tasmania), and type of stroke (ischaemic, haemorrhagic, TIA, other). The statistician will be blinded to the treatment group.

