### Recruitment and screening

AuSCR or HSRVR will screen individuals for eligibility criteria and will send out invitation packs on behalf of the trial research team to potentially eligible database registrants (i.e. individuals 6 to 36 months post first stoke, aged 18 years and older). Invitation packs will include a cover letter from AuSCR or HSRVR, a participant information statement describing the project Additional file 2 (Model participant information statement), and two consent forms (one for study participation Additional file 3 (Model participant consent form) and one to allow the researchers to access the individual’s health care data (Medicare and Pharmaceutical Benefits Schemes; MBS and PBS) from the national registry). Participants will be asked to sign and return the consent forms in a replied, paid envelope to the research team. Due to potential physical limitations in the population being studied, carers will be able to consent on behalf of individuals by signing the consent form and indicating that they are a carer. Upon receipt of the signed consent forms, potential participants will be telephoned by the research team (enrolment call) to be screened regarding Internet and email access, and disability using the brief nine-item modified Rankin Scale. Potential participants will be, given an opportunity to ask questions about the study. Upon eligibility confirmation, participants will complete a baseline CATI after which they will be randomised.

Figure 1 outlines study recruitment and follow-up, while Fig. 2 contains an assessment schedule for the trial. To promote adherence to programme use and study follow-up, both groups will receive reminder texts (intervention fortnightly with additional email reminder; control monthly) during the intervention period of 12 weeks, then both groups will receive monthly reminder texts, including the approximate date for their next survey, until the 6-month follow-up. Intervention participants will have access to P2S for the 12 weeks. After 11 weeks, intervention participants will receive an email notifying them that their access to the P2S programme will expire within a week. Survival checks will be completed with AuSCR or HSRVR prior to telephone contact. All participants will be asked to complete a 6-month follow-up CATI. Participants will be reimbursed with an AU$50 gift card after the completion of the 6-month survey.

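### The disability exclusion runs the wrong way: barring modified Rankin scores of 3 or below removes the least disabled people and keeps those it is meant to exclude

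*Protocol article*

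**What the plan says.** The Exclusion criteria section opens with "Individuals will not be eligible to participate in the study if they" and then gives two grounds. The second is that people "experience disability at a level that may limit their use of the programme (determined using a score of ≤" 3 "on the modified Rankin Scale"). One sentence therefore holds both the reason for the exclusion and the score that triggers it.

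Recruitment and screening says when the rule is applied. After signed consent is received, the research team telephones the person and screens for Internet and email access and for "disability using the brief nine-item modified Rankin Scale". That section repeats neither the cut-off nor the direction of scoring.

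Two other sections describe who the trial expects to enrol. Eligibility criteria admits people after a "first episode of care for acute stroke or TIA (indexed stroke event"), and asks for adequate facility with the Internet on a home device or that they "are willing to use public Internet services (e.g. public library"). Randomisation stratifies by "type of stroke (ischaemic, haemorrhagic, TIA, other").

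**The concern.** The purpose is to keep out people too disabled to use an online programme. A threshold that serves it must exclude the upper end of a scale on which higher means worse. The printed threshold excludes the lower end.

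This is the operative rule that decides who is randomised and to whom the results apply. Followed literally, it would enrol the opposite population to the one described. It would also leave the assumptions behind the sample size (a standard deviation of 24 points, a baseline to follow-up correlation of 0.6 and a 6-point difference) attached to a population they were not meant for. If screeners applied some other rule, the article misreports the trial population, and a reader cannot recover the true one.

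**Working it through.** This is a check of logic rather than of a calculated figure.

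**Inputs**

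- Purpose (Exclusion criteria): exclude those who "experience disability at a level that may limit their use of the programme".
- Trigger (same sentence): a score of 3 or below.
- Effect of meeting the trigger: ineligible, from the lead-in and the section heading. It cannot be read as a condition for entry.
- Direction of the scale: 0 = no symptoms, rising to 5 = severe disability, with 6 = death. This is an assumption, because the article does not print it. It is the standard definition of the named instrument, and nothing in the article suggests reverse scoring.

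**Rule applied to the grades that a living person can have (0 to 5)**

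| Reading | Excluded | Admitted |
|---|---|---|
| As printed: exclude ≤ 3 | 0, 1, 2, 3 | 4, 5 |
| Reversed: exclude > 3 | 4, 5 | 0, 1, 2, 3 |
| Reversed: exclude ≥ 3 | 3, 4, 5 | 0, 1, 2 |

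As printed, 4 of 6 grades are removed, all at the less disabled end. Either reversal agrees with the stated purpose. The two differ only on a score of 3, and the article does not settle which was meant.

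**Consistency with the other sections**

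- People with TIA are eligible and form one of four stroke-type strata. If only grades 4 and 5 were admitted, that stratum could be expected to be nearly empty.
- Participants must be able to use the Internet or be willing to travel to a public facility to do so, and the Intervention section encourages use at least weekly. This fits poorly with admitting only the two most disabled grades.

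**Effect on the sample size arithmetic**

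None directly. With the article's inputs, the residual standard deviation is 24 × √(1 − 0.6²) = 19.2. The number per arm is 2 × (1.960 + 0.842)² × 19.2² / 6² ≈ 161, against the stated 160. No eligibility threshold enters the formula. The standard deviation and correlation are, however, properties of whichever population is actually enrolled.

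**The case against.** The strongest reply is that this is a slip in reporting. The purpose is stated clearly, any reader can tell which end of the scale is meant, and the cause is probably a reversed sign or an entry limit placed under exclusions. Neither the screening script nor the full protocol is shown, so nothing proves that the printed rule was ever applied. That stands: harm to the trial population is conditional, and this review does not claim that it happened. The slip nevertheless sits in the only place where the article states the threshold, and knowing the direction does not give the boundary. That an article condenses a protocol excuses omissions, not a rule stated wrongly.

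A second reply is that the direction of the scale is not in the article, and that the scoring of the brief nine-item version is not described. That is fair, and the direction is declared above as an assumption. If the version used were scored in reverse, the cut-off would agree with the purpose, but nothing in the article points that way.

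A third is that Internet use alone does not imply mild disability: carers may consent on a participant's behalf because of physical limitations, and carer involvement is recorded. That is also fair, so no claim is made here about how disability is distributed among registrants. Allowing for some disability still does not explain excluding people who have none.

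**Conclusion.** The concern holds and must be fixed. Under the standard direction of the modified Rankin Scale, the only premise not printed in the article, the exclusion as written contradicts its own purpose: it removes grades 0 to 3 and admits only 4 and 5. No other section corrects it, and the eligibility and stratification of people with TIA do not fit the literal rule. How many registrants would be affected, and whether anyone was screened by the printed rule, cannot be determined from the article. The nature of the error is an internal contradiction in an eligibility criterion, not a debatable choice of threshold.

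**What to change.** Reconcile the Exclusion criteria with the Recruitment and screening section:

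1. Restate the cut-off so that it agrees with the stated purpose, whether the cause was a reversed sign or an entry limit listed as an exclusion. The boundary is for the sponsor to state.
2. Say explicitly whether a score of 3 is in or out, and give the direction of scoring for the nine-item version. Use the same wording in both sections.
3. Check the script used at the enrolment call against the corrected rule, and compare the recorded score of everyone screened and enrolled with it. Report any participant enrolled, or person turned away, contrary to it.

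The text change is a line or less. The main cost is step 3: Trial status gives a recruitment start of 1 March 2018 and a protocol version dated 1 September 2018, so enrolment had begun six months before that version. The sample size calculation needs no change on this account, provided its assumptions were made for the population that the corrected rule admits.

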#### Withdrawal

If a participant wishes to withdraw consent, they will be able to at any point in time. They will be given the option to remove all their previously collected data or just remove consent for further data collection.

### Sample size

A sample of 160 individuals will be needed per treatment arm at follow-up to enable the detection of a 0.25 standard deviation difference (a 6-point difference) in HRQoL at 6 months with 80% power and 5% significance. This assumes a correlation between the baseline and follow-up HRQoL of 0.6, and a standard deviation of 24 points. Pilot data suggest that approximately 40% of participants recruited at baseline will complete follow-up at 6 months and, therefore, the research team aim to recruit 530 eligible consenting participants at baseline [27].

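### The recruitment target of 530 does not follow from the stated 40% completion: 40% of 530 leaves 106 per arm, not 160, with power of about 62% rather than 80%

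*Protocol article*

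**What the plan says.** All the figures stand in one paragraph, Methods/design, Sample size, of the protocol article:

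- Requirement: "A sample of 160 individuals will be needed per treatment arm at follow-up".
- Target difference: "detection of a 0.25 standard deviation difference (a 6-point difference) in HRQoL at 6 months", "with 80% power and 5% significance".
- Assumptions: "a correlation between the baseline and follow-up HRQoL of 0.6" and "a standard deviation of 24 points".
- Retention: "Pilot data suggest that approximately 40% of participants recruited at baseline will complete follow-up at 6 months". The same sentence presents the recruitment target of 530 as the consequence.

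The Abstract repeats the target: "A total of 530 adults will be recruited across one national and one regional stroke registry". The Randomisation section fixes 1:1 allocation. The Primary analysis section specifies a linear regression of the EQ-5D-5L score on treatment group and its baseline value, with the stratification variables as covariates. No other section gives a completion or attrition rate.

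**The concern.** The step from 160 completers per arm to 530 recruits works only if 40% are lost. The text says that 40% complete. One of the two statements must be wrong, and which one it is decides whether the trial has the power it claims for its primary outcome.

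If 40% completion is correct, the trial has a chance of about 38% of missing a true 6-point difference, not 20%. A null result would then be read as stronger evidence against the programme than it is. If 60% completion was meant, the design number stands, but the published retention assumption is wrong, and anyone comparing achieved follow-up with it would take a serious shortfall to be on plan.

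**Working it through.** **Inputs.** From Sample size: difference 6 points, SD 24, correlation 0.6, power 80%, significance 5%, 160 per arm at follow-up, 40% completing, 530 recruited. From Randomisation: 1:1 allocation. From Primary analysis: adjustment for baseline. The protocol does not state whether the test is one- or two-sided. Two-sided is assumed here, and it reproduces the stated 160.

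**1. Reproduce the 160 per arm.** With baseline adjustment the residual SD is 24 × √(1 − 0.6²) = 24 × 0.8 = 19.2 points. Then

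n per arm = 2 × (1.960 + 0.842)² × (1 − 0.6²) / 0.25² = 160.7.

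This rounds up to 161. At exactly 160 per arm the power is 79.8%. The stated 160 therefore reproduces, and the error lies in the inflation for loss to follow-up.

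**2. Inflate for loss.** Completers needed: 2 × 160 = 320.

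| Reading of the 40% | Calculation | Recruits needed |
|---|---|---|
| 40% complete (as written) | 320 / 0.40 | 800 |
| 40% lost, 60% complete | 320 / 0.60 | 533 |
| Stated target | – | 530 |

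Reaching 320 completers from 530 recruits needs 320/530 = 60.4% completion. The common mistaken inflation, multiplying by one plus the loss rate, gives 320 × 1.6 = 512, which does not produce 530 either.

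**3. Power with 530 recruits.** The standard error of the adjusted difference is 19.2 × √(2/n), and power is Φ(6/SE − 1.960).

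| | 40% complete | 60% complete |
|---|---|---|
| Completers | 530 × 0.40 = 212 | 530 × 0.60 = 318 |
| Per arm | 106 | 159 |
| SE (points) | 2.64 | 2.15 |
| Power for 6 points, normal approximation | 62.4% | 79.6% |
| Power for 6 points, noncentral t | 62.0% | 79.3% |

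**4. Difference detectable with 80% power at 106 per arm.** (1.960 + 0.842) × 2.64 ≈ 7.39 points, and 7.39/24 = 0.308 SD.

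**5. Other readings of the design.** A one-sided test on the change score needs 159 per arm, so it would also account for the 160. It is not the planned model, and at 106 per arm its power is still only 65%. The choice of model and sidedness therefore does not remove the discrepancy.

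**The case against.** The strongest reply is that this is a slip of wording. The target of 530 is almost exactly 320/0.60, so 40% was probably applied as the loss rate and described as the completion rate. On that reading the target, the analysis and the power all stand, and one phrase needs correcting. This is the likeliest explanation, and it means that the 62% is conditional: it applies only if the completion rate is true as written. What is certain is the inconsistency, not that the trial is underpowered. The pilot source is not available here, so the likely explanation cannot be confirmed, and under either reading the published text is wrong.

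A second reply is that the Primary analysis section plans multiple imputation, so non-completers still contribute. This does not rescue the figure. The protocol's own calculation counts individuals at follow-up, and imputation does not by itself restore the information lost with unobserved primary outcomes. With 60% missing, the result would also lean more heavily on the missing-at-random assumption.

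The word for approximation in the retention sentence cannot bridge 40% and 60.4%. Nor is this a detail left to a fuller document, since every figure is stated.

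One caution does stand: the protocol sets no formal retention threshold or action, so the harm from a wrong retention benchmark is indirect. The main consequence is for the power claim.

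**Conclusion.** The point holds. The recruitment target and the stated completion rate contradict each other: 320 completers at 40% completion need 800 recruits, and 530 recruits give 106 per arm. If 40% completion is literal, power for 6 points is about 62% instead of 80%, and the difference detectable with 80% power rises to about 7.4 points (0.31 SD). If 40% is the loss rate, 530 gives 159 per arm and 79–80% power, essentially as stated.

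These figures rest on the protocol's SD of 24 and correlation of 0.6, on baseline adjustment as planned, equal completion in the two arms, and a two-sided 5% test. The correction must be made because the stated justification for the primary-outcome sample size is false as written, and the reader cannot tell which half of it to believe.

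**What to change.** Check the completion rate in the pilot data, then correct the Sample size section in one of two ways.

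- **If 40% is the loss rate:** state that about 60% are expected to complete follow-up and 40% to be lost, so that 530 recruits give 318 completers (159 per arm) and about 79–80% power for 6 points.
- **If 40% is the completion rate:** keep 530 and restate what it supports: 212 completers (106 per arm), about 62% power for 6 points, or 80% power for 7.4 points (0.31 SD). Keeping both the 6-point target and 80% power would instead take 800 recruits. Whether that is feasible is for the sponsor to decide.

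In either case, say that the test is two-sided if that is what was used, and carry the correction into the statistical analysis plan if it repeats the sentence. The cost is a correction of wording and numbers with no extra participants, unless the sponsor chooses to raise the target. Under the second reading the stated power becomes less favourable.
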